### Data management and statistical analyses

The project was designed to allow change in outcome variables to be calculated for each participant using a pre-post experimental design. Measures were taken at baseline prior to exposure to intervention, then again following either 1 or 2 years of programming (Table 5). To achieve a balanced design, similar numbers of control and treatment participants were recruited into each of the three cohorts, and similar numbers of boys and girls were recruited into each treatment group (Table 3). Data for cohorts will be combined at the analysis stage.

**Table 5 T5:** *Taking Action Together *Project Plan - Project Timeline

Project Year^1^	**1**^3^				**2**^3^				**3**^3^				**4**^3^			
Develop program	A	B	C	D												
Refine program					A	B	C	D	A	B	C	D				
Convene Advisory Board		B				B				B				B		
Train staff			C	D	A	B	C	D	A	B	C	D	A	B	C	
Conduct process evaluation					A	B	C	D	A	B	C	D	A	B	C	D

Recruit study participants																
First cohort (n = 103)			C	D												
Second cohort (n = 63)							C	D								
Third cohort (n = 69)											C	D				

Provide intervention^2^																
First cohort					A	B	C	D	A	B	C	D	A			
Second cohort									A	B	C	D	A	B	C	D
Third cohort													A	B	C	D

Perform impact measures (0 = pre-study;1 = 1^st ^Yr follow-up; 2 = 2^nd ^Yr follow-up)^2^																
First cohort				0				1				2				
Second cohort								0				1				2
Third cohort												0				1

^1 ^Project began middle of 2004 and ended in middle of 2008.

^2 ^Quartiles of each study year are indicated as follows:  A, 1^st^ quartile; B, 2^nd^ quartile, C, 3^rd^ quartile, D, 4^th^ quartile.

^3^ The first and second cohorts were followed for a total of two years whereas the third cohort was followed only for a single year.

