#### Assessing bias due to motivation

The potential for bias due to motivation was estimated by comparing dropout rates between the two groups during the 1 or 2 year intervention period. Dropout rates for control and intervention groups were similar after both 1 year (40% versus 44%; p = 0.46) and 2 years (66% versus 72%; p = 0.52) of programming. Furthermore, when information collected at baseline was compared for dropouts from the control versus treatment groups, no significant differences were found. As examples, mean baseline insulin resistance (HOMA-IR) values of children who dropped out of the control versus treatment groups during the first year were 2.61 and 2.76, respectively (p = 0.67), and means for dropouts during two years of programming were 2.59 and 2.55, respectively (p = 0.91). Additionally, baseline insulin resistance values for children who completed two years of programming versus those who did not were not significantly different (HOMA-IR mean values: 2.56 and 2.53, respectively; p = 0.90).

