**Figure 2 F2:**
[figure not shown]
**Flowchart of study participant recruitment, self-selection to site, and eligibility assessment**.

At the analytical stage, statistical analyses for differences by treatment group will be controlled, if needed, for covariates including child age, gender, socioeconomic status, pubertal stage or other potential anthropometric, dietary, physical activity, self esteem, behavior or family confounders (for a comprehensive list of variable assessed, refer to Table 1). The necessity for adjustment for a particular variable will be determined in a preliminary analysis in the following way. Any variable modestly related (p < 0.25) to BOTH treatment group status and the change in the outcome variable will be considered to be a potential confounder and included in analytic models. Since subjects were not randomized into groups, analyses will be statistically adjusted for baseline outcome values (analysis of covariance) as groups may not have been equivalent at baseline for these outcomes (some examples are shown in Table 4).

**Table 4 T4:** Some baseline characteristics of participants in the control and intervention groups (p-value for difference by group).

	Characteristic	Control (mean)	Intervention (mean)	p-value
Child	Age (yr)	9.84	9.85	0.92
	BMI z-score	2.00	2.05	0.52
	Waist-to-hip ratio	0.88	0.89	0.36
	% body fat	36.2	36.3	0.90
	Pubertal stage (1-5 scale)	2.28	2.17	0.54
	Fasting HbA1c (%)	5.18	5.14	0.44
	Fasting HOMA-IR	2.49	2.51	0.94
	Fasting ISI-FFA	0.43	0.42	0.72
	Energy intake (kcal/day)	1829	1887	0.53
	Fat intake (g/day)	75.2	73.0	0.62
	Carbohydrate intake (g/day)	220	245	0.04
	Protein intake (g/day)	71.5	67.9	0.38
	Whole grains intake (servings/day)	0.70	0.73	0.77
	Fruit & vegetable intake (servings/day)	2.06	2.38	0.10
	Dairy intake (servings/day)	1.27	1.21	0.59
	Nutrition knowledge (1-22 scale)	9.63	9.96	0.25
	Food preferences (7-25 scale)	16.0	16.3	0.32
	Snack habits (1-5 scale)	2.41	2.45	0.76
	Fitness (ml O2/min/kg body wt)	41.8	43.8	0.26
	Moderate- & high-intensity physical activity (min/day)	89.7	104.4	0.31
	Global self-worth (1-4 scale)	2.98	3.04	0.55
	Athletic competence (1-4 scale)	2.76	2.82	0.47
Family or Adult	Age of adult responder (yr)	37.1	38.5	0.30
	SEI (4-12 range)	8.42	8.29	0.59
	Family History of T2DM (0-2 scale)	0.13	0.20	0.18
	Intrauterine risk for T2DM (0-2 scale)	0.34	0.32	0.82
	Food habits (7-36 scale)	21.9	23.0	0.04
	Physical activity habits (3-15 scale)	11.7	12.2	0.28

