#### Quantitative data

Quantitative data were managed using computer programs including Microsoft Excel, EpiData, BASC-2 software [34], USDA Nutrient Database [35] and MyPyramid Equivalents Database [36]. Data were double entered and edit checks were incorporated into the data entry program to identify data entry errors. For psychosocial, knowledge and attitude measures, scales will be developed as necessary and compared as described above.

Mean changes in the quantitative outcome variables of interest (HOMA-IR and secondary anthropometric, dietary and activity variables) over one or two intervention years will be evaluated using multiple regression techniques. Adjustment for multiple comparisons will not be made, and with values for p < 0.05 considered statistically significant [37]. In addition, because some of these outcome measures are considered to be intermediary or confounding variables, we will use multiple linear regression to examine the effect of intervention on the primary outcome variable of interest (HOMA-IR), adjusting for baseline HOMA-IR, BMI z-score, psychosocial measures such as self esteem, diet and physical activity behaviors, and other potentially relevant factors such as family and (to account for genetic differences in response to intervention) intrauterine history of T2DM. The correlations of all potential covariates with both the dependent and independent variables will be examined, and variables that correlate at p < 0.25 with both variables will be included in the models.

Initially, we will examine the regression coefficient for intervention status (a dummy variable where 1 = intervention group, 0 = control group) in a simple regression model. Using change in HOMA-IR as one dependent variable example, we will model as follows:

Next, we will examine the effects of other explanatory and/or confounding variables to determine whether they explain the effects of intervention status (if any) using as an example:

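### The two-year analysis drops at least 35 children whose year-1 values are held, and the reported dropout checks cannot exclude outcome-related loss; a repeated-measures model would help at year 2 only

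*Protocol article*

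**What the plan says.** Data management and statistical analyses sets the outcome as change per child ("The project was designed to allow change in outcome variables to be calculated for each participant using a pre-post experimental design") and adds "Data for cohorts will be combined at the analysis stage". Under Quantitative data, mean changes "over one or two intervention years will be evaluated using multiple regression techniques". The intervention indicator is examined first "in a simple regression model" and then with covariates. Reducing bias due to non-randomization adds that "analyses will be statistically adjusted for baseline outcome values (analysis of covariance").

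A note to Table 5 says who was due when: "The first and second cohorts were followed for a total of two years whereas the third cohort was followed only for a single year".

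Assessing bias due to motivation offers three checks:
- Dropout rates: "The potential for bias due to motivation was estimated by comparing dropout rates between the two groups", with rates called similar "after both 1 year (40% versus 44%; p = 0.46) and 2 years (66% versus 72%; p = 0.52) of programming".
- Baseline HOMA-IR of control and intervention dropouts: 2.61 and 2.76 in the first year (p = 0.67), 2.59 and 2.55 over two years (p = 0.91).
- Baseline HOMA-IR of two-year completers and non-completers, arms pooled: 2.56 and 2.53 (p = 0.90).

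**The concern.** A child without the follow-up value has no change score and leaves the model. The same holds for analysis of covariance (ANCOVA), so the loss comes from needing that follow-up value, not from change scores as such. For the two-year effect the plan therefore also ignores year-1 values already collected on children who later left. Those values are the best information held on how these children were doing.

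If intervention children who were not improving left more readily than similar controls, the two-year comparison of those remaining would favour the intervention. Similar dropout rates do not exclude this, because two arms can lose equal numbers of different children. Comparisons of baseline values do not exclude it either, because they say nothing about response after baseline.

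**Working it through.** **Inputs.** Table 3: baseline 111 control and 124 intervention (cohorts 1 and 2: 51 + 28 = 79 and 52 + 35 = 87). Year 1: 67 and 69 (cohorts 1 and 2: 33 + 20 = 53 and 37 + 18 = 55). Year 2: 38 and 35. Statistical power and sample size: SD 7.2 μU/ml, baseline-to-final correlation 0.6, difference 4 μU/ml.

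**1. The plan's dropout rates.**
- Year 1: 44/111 = 39.6% and 55/124 = 44.4%, chi-square p = 0.465. This reproduces the stated figures.
- Year 2: (111 − 38)/111 = 65.8% and (124 − 35)/124 = 71.8%. The stated 66% and 72% appear only when the 32 + 37 = 69 cohort-3 children count as dropouts.
- Among those due: (79 − 38)/79 = 51.9% and (87 − 35)/87 = 59.8%.
- The stated two-year p = 0.52 does not reproduce. Chi-square gives 0.32 on all children and 0.31 on those due (0.39 for both with continuity correction).

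**2. How much the rate check can exclude.** The 95% interval is d ± 1.96 √(p₁q₁/n₁ + p₂q₂/n₂). The difference, intervention minus control, is 4.7 points (−7.9 to 17.3) at year 1 and 7.9 points (−7.2 to 23.0) at year 2 among those due.

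**3. Do the reported means fit together?** Any pooling of dropout means 2.59 and 2.55 lies between those two values; weighting by 73 and 89 gives 2.57. The non-completer mean is printed as 2.53. Completers (2.56) and non-completers (2.53) also both exceed the Table 4 arm means of 2.49 and 2.51. Differing denominators might explain this, but none are stated.

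**4. Who is used.** Year 1: 136/235 = 57.9%. Year 2: 73/166 = 44.0%. In cohorts 1 and 2, 53 + 55 = 108 children have a year-1 value, so at least 108 − 73 = 35 are left out of the two-year result. A joint model raises the children in these cohorts who inform that result from 73 to 108 of 166 (65%), plus 28 from cohort 3. The 235 − 136 = 99 without a year-1 value remain unrecovered.

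**5. Precision.** With s = 7.2 √(1 − 0.6²) = 5.76:
- Year 1, ANCOVA: 5.76 √(1/67 + 1/69) = 0.988. The repeated-measures model also gives 0.988. Unadjusted change gives 7.2 √0.8 × √(1/67 + 1/69) = 1.105.
- Year 2, ANCOVA: 5.76 √(1/38 + 1/35) = 1.349. Unadjusted change gives 1.509.
- Year 2, repeated measures: s √{Σ over arms [(1 − ρ²)/n₂ + ρ²/n₁]}. Here n₁ and n₂ are the year-1 and year-2 counts, and ρ = (r₁₂ − 0.36)/0.64 is the year-1 to year-2 correlation given baseline. The documents do not give r₁₂. Assuming r₁₂ = 0.4, 0.6 and 0.8 gives ρ = 0.0625, 0.375 and 0.6875, and standard errors of 1.348, 1.305 and 1.192. These are 0.1%, 3.3% and 11.6% below ANCOVA.
- Power for 4 μU/ml at year 2, Φ(4/SE − 1.96): 75.5% for unadjusted change, 84.2% for ANCOVA, and 84.3%, 86.6% and 91.8% for repeated measures.

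These figures assume that every child seen at year 2 was also seen at year 1.

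**6. Bias with no true effect.** Simulated in SD units, all correlations 0.6, selection in the intervention arm only with a dropout log odds ratio of 0.8 per SD. Negative values falsely favour the intervention.
- Dropout on baseline: unadjusted change +0.12; ANCOVA and likelihood model about 0.
- Year-2 dropout on the observed year-1 value: ANCOVA −0.06 at year 2; likelihood model about 0. Unadjusted change is also near 0, because the correlations were set equal.
- First-year dropout on a year-1 value never seen: ANCOVA and likelihood model both −0.20 at year 1 and −0.07 at year 2.

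A second simulation used HOMA-IR units. Its SD of 1.74 is back-calculated from the dropout comparison: p = 0.67 gives z = 0.426, so SE = 0.15/0.426 = 0.352, and 0.352/√(1/44 + 1/55) = 1.74. With dropout odds ratios of 2.0 to 2.7 per SD in the intervention arm, completers-only ANCOVA was biased by 0.09 to 0.13 units. With opposite selection in controls the bias was 0.16, about half its standard error of 0.323. The likelihood model stayed within 0.007.

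**The case against.** **Scope.** Missing-data handling is often left to a full protocol or analysis plan, and neither is at hand. That is fair for anything merely absent. But the article itself fixes regression on individual change and presents its dropout checks as reassurance, and the point rests on those two statements.

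**Baseline differences.** A reader might infer from the printed means that sicker intervention children left. If HOMA-IR was known for all at baseline, year-1 completers averaged (111 × 2.49 − 44 × 2.61)/67 = 2.41 in control and (124 × 2.51 − 55 × 2.76)/69 = 2.31 in intervention. They fall below dropouts by 0.20 and 0.45. The documents do not support that reading. With SD 1.74 the standard errors are 0.34 and 0.31, and the gaps differ by 0.25 (SE 0.46, p about 0.59). They are also baseline gaps, which the planned ANCOVA handles. The article does report a completer contrast, though it pools the arms and uses baseline only.

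**Cohorts.** Year-1 attrition differs by cohort (33/103 = 32%, 25/63 = 40%, 41/69 = 59%), so a reader might suspect that pooling confounds the result. Year-1 completers are nearly balanced by arm (33:37, 20:18, 14:14), and combining cohorts does not rule out a cohort term. Little confounding can arise this way. Cohort 3's absence at year 2 is by design.

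**The remedy.** A reader might think that a mixed model repairs the 42% loss at year 1, or cures selective dropout generally. It does neither. Children with baseline only carry no information on the effect, and all methods share the bias when the driving value was never observed. This part of the objection stands and limits the claim.

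**Conclusion.** The concern holds in limited form. The retention counts are exact. The reported checks cannot exclude outcome-related dropout: they are non-significant comparisons of rates and baseline values, one set of means does not fit the others, and the two-year rates use a denominator that includes children never due.

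The benefit of a joint model is confined to year 2. The standard error falls by about 0 to 12% over assumed year-1 to year-2 correlations of 0.4 to 0.8. Bias is removed only if dropout depends on observed values. That bias is at most about half a standard error, under odds ratios that are assumptions and not figures from the document. Nothing in the article shows that the result is in fact biased towards the intervention. This is a worthwhile improvement to the plan, not a defect that invalidates it.

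**What to change.** - Take the year-2 effect from a likelihood-based repeated-measures model of the year-1 and year-2 values. Include arm by visit, baseline HOMA-IR by visit and cohort as a fixed effect, with unstructured covariance, and use every child with any follow-up.
- Keep completers-only ANCOVA as a supportive analysis.
- Add one multiple-imputation sensitivity analysis with an increasing penalty for intervention dropouts, and report the penalty at which the conclusion changes. This covers dropout driven by unseen values, which the model does not.
- Restate two-year dropout among the 166 due (51.9% and 59.8%), recheck the p-value, and reconcile the completer and dropout means with stated denominators.

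The cost is one standard mixed model and one imputation run on data already held. The model assumes missing at random. Lessons learned reports that one-year glucoregulation results have already been analysed, so the model must be labelled as a change made after that.

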#### Quantitative data

Quantitative data were managed using computer programs including Microsoft Excel, EpiData, BASC-2 software [34], USDA Nutrient Database [35] and MyPyramid Equivalents Database [36]. Data were double entered and edit checks were incorporated into the data entry program to identify data entry errors. For psychosocial, knowledge and attitude measures, scales will be developed as necessary and compared as described above.

Mean changes in the quantitative outcome variables of interest (HOMA-IR and secondary anthropometric, dietary and activity variables) over one or two intervention years will be evaluated using multiple regression techniques. Adjustment for multiple comparisons will not be made, and with values for p < 0.05 considered statistically significant [37]. In addition, because some of these outcome measures are considered to be intermediary or confounding variables, we will use multiple linear regression to examine the effect of intervention on the primary outcome variable of interest (HOMA-IR), adjusting for baseline HOMA-IR, BMI z-score, psychosocial measures such as self esteem, diet and physical activity behaviors, and other potentially relevant factors such as family and (to account for genetic differences in response to intervention) intrauterine history of T2DM. The correlations of all potential covariates with both the dependent and independent variables will be examined, and variables that correlate at p < 0.25 with both variables will be included in the models.

Initially, we will examine the regression coefficient for intervention status (a dummy variable where 1 = intervention group, 0 = control group) in a simple regression model. Using change in HOMA-IR as one dependent variable example, we will model as follows:

Next, we will examine the effects of other explanatory and/or confounding variables to determine whether they explain the effects of intervention status (if any) using as an example:

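### The intervention effect on HOMA-IR is first read from a simple regression of change, although the article elsewhere requires baseline adjustment, and no model is named as the one that answers aim 1

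*Protocol article*

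**What the plan says.** Two sections of the protocol article describe how the treatment effect will be estimated.

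- **Reducing bias due to non-randomization.** The rule on baseline is unconditional: "analyses will be statistically adjusted for baseline outcome values (analysis of covariance) as groups may not have been equivalent at baseline for these outcomes". The qualifier about need applies to the other covariates. These enter the analytic models by a screening rule: "Any variable modestly related (p < 0.25) to BOTH treatment group status and the change in the outcome variable".
- **Quantitative data.** HOMA-IR is to be examined by multiple linear regression, "adjusting for baseline HOMA-IR, BMI z-score, psychosocial measures such as self esteem, diet and physical activity behaviors, and other potentially relevant factors". The steps are then set out in order. The first is: "Initially, we will examine the regression coefficient for intervention status", coded 1 for intervention and 0 for control, in what the article calls a simple regression model. The dependent variable is change: "Using change in HOMA-IR as one dependent variable example, we will model as follows". The equation that follows is not in the text available. The next step adds other explanatory or confounding variables, to see whether they account for any intervention effect.

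The same section sets p < 0.05 and makes no adjustment for multiple comparisons. Aim 1, under Hypotheses and specific aims, concerns the influence of group on change in HOMA-IR. No section says which coefficient answers it.

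**The concern.** A simple regression on one 0/1 variable has a single predictor. Read that way, the first look at the intervention effect omits the baseline term that the other section requires because the groups were not randomised. The same outcome at the same visit can then be tested without and with baseline, each at p < 0.05.

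Two things are at stake. If either result may be taken as the trial's answer, the type I error exceeds 5%. If the simple model is taken, precision is lost that baseline values, already collected, would supply.

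The adjusted models add a question of meaning. Quantitative data describes some of the variables as intermediary, and the hypotheses place diet, activity and self-esteem on the path to insulin resistance. If changes in those variables enter the model, its coefficient is no longer the total effect of the intervention.

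**Working it through.** **Inputs.** From Statistical power and sample size: difference 4 μU/ml, SD 7.2 μU/ml, correlation r = 0.6 between initial and final values, alpha 0.05, power 0.80, 50 per group. From Table 3: 67 control and 69 intervention at 1 year; 38 and 35 at 2 years. From Table 4: baseline HOMA-IR 2.49 and 2.51. Assumptions: two-sided tests, equal SDs at both visits, and the insulin inputs standing in for HOMA-IR, for which no SD is given.

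**Step 1: does the sample size show which model was meant?** n per group = 2 × (1.96 + 0.8416)² × SD² / 4².

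| Analysis | SD used | n per group |
|---|---|---|
| Final values, r ignored | 7.2 | 50.9, so 51 |
| Change | 7.2 × √(2 × 0.4) = 6.44 | 40.7, so 41 |
| ANCOVA | 7.2 × √(1 − 0.36) = 5.76 | 32.6, so 33 |

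The stated 50 is close to the first row only. It matches neither candidate model, so it does not settle the question.

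**Step 2: relative precision.** Variance ratio of ANCOVA to change = (1 − r²) / (2(1 − r)) = (1 + r) / 2 = 0.80.

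**Step 3: type I error if either model counts.** With no true effect, the correlation of the two test statistics is √((1 + r)/2) = √0.80 = 0.894. The bivariate normal probability that at least one exceeds 1.96 in absolute value is 0.071. For r = 0.4 and r = 0.8 it is 0.076 and 0.065. Simulation at r = 0.6 gives 6.8% to 7.2% at 67/69 and about 7.0% at 38/35, with each model alone at about 5%.

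**Step 4: power for 4 μU/ml.** SE = SD × √(1/n₁ + 1/n₂); power = Φ(4/SE − 1.96).

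| Numbers | Model | SE | Power |
|---|---|---|---|
| 67/69 | Change | 1.105 | 95.2% |
| 67/69 | ANCOVA | 0.988 | 98.2% |
| 38/35 | Change | 1.509 | 75.5% |
| 38/35 | ANCOVA | 1.349 | 84.2% |

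Simulation with t tests gives about 74.5% and 83% at 38/35. The two models then disagree on significance in about 13% of trials. At 67/69 they disagree in about 4%.

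**Step 5: shift in the estimate.** The change contrast and the ANCOVA contrast differ by (1 − slope) × baseline difference. With slope 0.6, HOMA-IR gives 0.4 × (2.51 − 2.49) = 0.008. This uses whole-sample means; baseline means by group for children with follow-up are not given.

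**The case against.** The strongest reply is that the equation is missing, so the absence of a baseline term is an inference. The section also opens by promising multiple regression with baseline HOMA-IR, and the ordered steps look like ordinary model building. No sentence says that success in any one model is enough. In addition, an article may leave the naming of the deciding model to an analysis plan.

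Part of this stands. The reading rests on prose, and the 7% applies only if either result could be claimed. But the order of the steps does not say which one decides, and the printed wording conflicts with the printed baseline rule. That is more than a missing detail.

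Several stronger readings are tempting, and the article does not support them:

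- **Three separate tests with still higher error.** The article does not list a model with only group and baseline as its own test. The two adjusted descriptions share one screening rule and may be one model. Any figure for a third model needs the variance explained by the covariates, which is not given.
- **The change analysis leaves baseline uncorrected.** A change score subtracts baseline in full. It differs from ANCOVA in how much it adjusts, and in self-selected groups ANCOVA is not automatically the unbiased reference.
- **The HOMA-IR result is materially biased.** The shift expected from Table 4 is about 0.008. Some dietary outcomes differ more at baseline: carbohydrate by 245 − 220 = 25 g/day, which would shift the contrast by 0.4 × 25 = 10 g/day. That borrows r = 0.6 from insulin; assumed slopes of 0.8 to 0.4 give 5 to 15 g/day.
- **Confounder-adjusted models should be only supportive.** The article requires qualifying confounders in its analytic models, and in a non-randomised two-site study that safeguard should stay.

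**Conclusion.** The concern holds as a conflict between two sections over the baseline term, together with no named deciding coefficient for aim 1. The loss is modest but avoidable. Type I error is about 7% if either of two models may count. At 2 years the choice of model decides whether the planned 80% power is met; at 1 year it matters little for the planning effect. These figures assume r = 0.6, two-sided tests and the insulin inputs. The change should be made, but the conflict does not by itself invalidate the trial's result.

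**What to change.** Under Quantitative data, include the baseline value of the outcome in the first model, as the section on non-randomization already states, and do the same for every outcome. State that the baseline-adjusted intervention coefficient with its 95% CI decides aim 1, and that its model includes the pre-intervention confounders required in analytic models. Report the unadjusted comparison of change as descriptive. Report models that add intermediary variables (changes in diet, activity or self-esteem) as explanatory only.

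This needs a few sentences, no new data, and one degree of freedom for the baseline term. The cost is that a significant result from another model can no longer be claimed as the trial's answer. The Discussion already reports 1-year glucoregulation findings, so where results have been seen the choice must be reported as made afterwards.
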